#### Sample size

The sample size is based on a recent retrospective cohort study which investigates the length of hospital stay in older people living with dementia by matching people without dementia in Germany [63]. We assume a mean reduction in the length of hospital stay of three days (intervention vs. control). With a standard deviation of 18 vs. 16 days, an intraclass correlation coefficient of 0.05 [64], and three clusters per treatment group with 120 people with cognitive impairment each, the adjusted two-sample t-test will reach a power of 81.5% at one-sided significance level of 50% [65]. Thus, this exploratory trial will be sufficiently powered to show the hypothesized direction of effect only.

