#### Data analysis

Statistical analysis is according to intention-to-treat (no exclusions). We will evaluate the primary outcome length of hospital stay by the stratified log-rank test (death is censored). Nota bene, the stratified log-rank test has very similar characteristics as the stratified van-Elteren rank-sum test and is available in many (statistical) software packages. We will use a propensity score approach (PSA) to balance individual characteristics between participants in intervention and control groups. In the multivariable logistic regression for PSA, we will use the independent variables age, gender, severity of cognitive impairment, Charlson Comorbidity Index, admission type, expected admission diagnosis-related or ward-related length of stay, and hospitalisations during the last 7 days [66, 67] as these variables are likely to be associated with outcome. Moreover, we will carefully monitor mortality in both arms, although we do not expect any difference. We will evaluate secondary outcome measures by (generalised) mixed models for repeated measures over time. If feasible, we will take outcome measures (particularly those reported by people with cognitive impairment) over the course of hospital stay. Thus, we may need to evaluate the outcome trajectories by random coefficient models. We will categorise and compare safety outcomes by frequency, relatedness, seriousness, and severity. Moreover, we will summarise variables by mean, standard deviation, and percentiles (0, 25, 50, 75, and 100) respectively by absolute and relative frequencies (percentage). Due to the small number of clusters, we will at least account for them in a fixed effect analysis. Though we will attempt to estimate corresponding random effects (e.g., to derive intraclass correlation), this seems prone to bias.

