#### Data analysis

In the cost-consequence analysis, we will compare the intervention group with the control group in terms of total inpatient costs, length of hospital stay, and cost weight. We will add the intervention costs (e.g., training costs) to the DRG charges of the intervention group. We will analyse differences (possibly after log-transformation) between the mean total costs using a t-test. In addition, we will perform additional analyses according to gender, age groups, and cost weight using t-test, Mann–Whitney-U-test, and other statistical tests. The analysis will be performed with IBM SPSS [74] and Microsoft Access.

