## Discussion

Complex interventions are considered most promising in promoting PCC [76]. The ENROLE-acute intervention builds on implementing an expanded nursing role as a core element to enhance PCC for people with cognitive impairment in acute care. Intervention development and testing are theory-based and follow recent guidance [26, 69]. The planned exploratory CCT will provide insights into the intervention’s initial effects, with the primary outcome focusing on patient length of hospital stay. Since there is a lack of high-quality studies to evaluate PCC interventions for people with cognitive impairment using expanded nursing roles in acute care, our study will provide important evidence. With the accompanying mixed-methods process evaluation, we will additionally examine the intervention’s implementation, mechanisms of change, and contextual factors. Analysing these underlying processes will lead to more transparency in trial results and a comprehensive understanding of how and under what circumstances the intervention will actually work. The additional economic analysis will increase our knowledge regarding the costs of the intervention.

However, some limitations of the study must be considered. Due to practical reasons, randomisation of the clusters will not be feasible. This may lead to differences between the groups at baseline resulting in a high risk of selection bias. However, we will consider these differences in the statistical analyses. Due to the nature of the intervention, blinding of participants and researchers during the study period will also not be possible. The knowledge of the group allocation might affect both the participants’ answers and data collection by researchers. At least the statistician will be blinded during data analysis. Finally, staff turnover during the six-month intervention period might result in differences between staff participating in the data collection at baseline and follow-up.

Despite the limitations, the study results will support the future development and implementation of new as well as the optimisation of existing PCC interventions based on expanded nursing roles. Our implications can particularly inform evidence-based decision making at the management and policy level. Additionally, our results will provide valuable information for planning and conducting large-scale trials as claimed in the third and fourth stage of the MRC guidance [26].

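### The cost comparison names a simple t-test, without the propensity score or ward allowance that the effect evaluation uses for the same non-randomised wards

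*Protocol article*

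**What the plan says.** The Data analysis section under Economic evaluation sets out a comparison of the arms on total inpatient costs, stay and cost weight, with intervention costs added to the DRG charges of the intervention arm. A test is named for costs: "We will analyse differences (possibly after log-transformation) between the mean total costs using a t-test". Further work follows: "In addition, we will perform additional analyses according to gender, age groups, and cost weight using t-test, Mann–Whitney-U-test, and other statistical tests". No propensity score, covariate model or ward term appears, and the section does not refer back to the effect evaluation.

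The Data analysis section under Evaluation of effects is different. It says "We will use a propensity score approach (PSA) to balance individual characteristics between participants in intervention and control groups", and it commits to handling wards at least as fixed effects.

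Both evaluations use the same six wards. Under Assignment of intervention, a ward's arm followed from its manager's choice. The Discussion accepts that this creates a serious risk of selection bias and adds: "However, we will consider these differences in the statistical analyses". That sentence is not limited to the primary outcome.

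**The concern.** Potential cost savings are objective (c) of the study, and the Discussion expects the results to inform management and policy decisions. Two features of the design bear on any cost comparison.

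- **Confounding.** Wards that volunteered may treat different patients, at different cost, from wards that did not. A plain t-test attributes that difference to the intervention.
- **Clustering.** Patients on one ward share case mix, staffing and discharge practice. A test that treats them as independent understates the standard error.

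The effect evaluation addresses both features, and the cost evaluation as written addresses neither. Analysing costs by gender, age group and cost weight does not fill the gap, because it adjusts neither for ward nor for the other variables in the propensity model.

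A smaller point concerns the optional log-transformation. A t-test on log costs compares geometric means, whereas a saving from the hospital's perspective is a difference in arithmetic means. The two can disagree when the spread of costs differs between arms.

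**Working it through.** **Inputs.** From Sample size: "an intraclass correlation coefficient of 0.05"; "three clusters per treatment group with 120 people with cognitive impairment each"; standard deviations of 18 and 16 days; a 3-day difference; one-sided level 50%; stated power 81.5%. All of these refer to length of stay. No ICC or significance level is given for costs.

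**1. Reproduce the plan's own figure.**
- Design effect: 1 + (120 − 1) × 0.05 = 6.95.
- Standard error: √[(18² + 16²)/360 × 6.95] = 3.346 days.
- Power: Φ(3/3.346 − 0) = 0.8150, as stated. The critical value is zero at a one-sided 50% level.

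The protocol's sample size therefore already rests on a design effect of 6.95.

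**2. False-positive rate of a t-test that ignores wards.** Assume a two-sided 5% level and 120 patients per ward. With no true effect and no confounding, the rate is 2 × [1 − Φ(1.96/√DE)].

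| Assumed ICC for cost | Design effect | False-positive rate |
|---|---|---|
| 0.005 | 1.59 | 12.1% |
| 0.01 | 2.19 | 18.5% |
| 0.02 | 3.38 | 28.6% |
| 0.03 | 4.57 | 35.9% |
| 0.05 | 6.95 | 45.7% |
| 0.10 | 12.90 | 58.5% |

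At ICC 0.05: 1.96/√6.95 = 0.743, and 2 × [1 − Φ(0.743)] = 0.457.

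**3. Sensitivity at ICC 0.05.**
- Smaller wards: 25.4% with 40 patients per ward, 32.4% with 60, 37.8% with 80.
- One-sided 5% level, 120 per ward: 26.6%.
- Simulation, 10,000 null trials per setting: 46.4% for normal data and 40.7% for skewed, untransformed lognormal data (an assumed shape).

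**4. Ward-level alternative.** A t-test on the six ward means, with 4 degrees of freedom, gave 5.1% in the same normal-data simulation.

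**5. What that alternative costs in precision.** With the length-of-stay inputs, a 95% interval on 4 degrees of freedom has half-width 2.776 × 3.346 = 9.3 days, around a planned effect of 3 days. Costs may behave differently, but a similarly wide interval should be expected.

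**6. Data needed for adjustment.** The claims variables listed under Economic evaluation do not include severity of cognitive impairment, admission type or recent hospitalisations, all of which enter the propensity model. The list need not be complete: it omits age, yet analyses by age group are planned. No link to the trial data is described.

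**The case against.** The best defence is that this is a condensed article about an exploratory feasibility study, powered only to show the direction of effect. The economic section sets no decision rule, leaves room for other tests, and could be covered by the Discussion's general promise to take baseline differences into account. A fuller economic plan may contain the adjustment.

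Part of this stands. The exploratory aim lowers the severity, and the Discussion's promise is too general to call the t-test a broken commitment. It does not remove the point, because the article names a specific method for costs, and that method lacks the two features that the same article considers necessary for its effect evaluation.

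A reader might also infer several stronger things that the text does not support:

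- **A false-positive rate of 46% as a fact.** It depends on carrying the length-of-stay ICC over to costs and on a two-sided 5% level; the economic section states neither.
- **A second t-test of the primary outcome.** The t-test is tied to mean total costs. For length of stay the section says only that the arms will be compared, and setting consequences beside costs is what a cost-consequence analysis does.
- **Mann–Whitney tests of mean cost.** That test is listed only for the additional analyses.
- **Published intervals that are too narrow.** The section mentions no intervals.
- **A fixed decision to use log costs.** The transformation is only a possibility.

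**Conclusion.** The point holds in this limited form and should be fixed. The named cost test includes neither the confounding adjustment nor the ward allowance of the effect evaluation, although the allocation problem is identical. That it ignores wards is a reading of the section, which names no ward-level step.

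Under the assumptions stated above, clustering alone raises a nominal 5% error rate to about 46%, with a range of about 19% to 59% for ICCs of 0.01 to 0.10. Even at 0.01 the rate is more than three times nominal. Confounding by ward choice adds to this, and the documents give no basis for quantifying it. The primary analysis is not affected.

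**What to change.** In the Data analysis section under Economic evaluation:

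1. Apply the propensity-score approach of the effect evaluation to the cost comparison.
2. State that the pseudonymised claims file carries a participant code and a ward identifier, so that the propensity variables can be merged and wards taken into account.
3. Report the difference in arithmetic mean cost with a ward-aware interval, for example at ward level on 4 degrees of freedom. Present it as an estimate and not as a significance test.
4. Do not base the cost-saving conclusion on a log-scale t-test.
5. Where length of stay is shown beside costs, use the estimate from the primary analysis.

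This costs some analysis wording and, if it is not already arranged, a linking code and ward identifier in the data transfer. It needs no extra patients. There is a real downside, which the protocol should state: with six wards the interval will be very wide, possibly too wide to say whether money is saved, and patient-level propensity scores cannot remove confounding that acts at ward level.

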## Objectives

This study aims to test the feasibility and clinical effectiveness of the newly developed PCC intervention. Therefore, our objectives are to assess (a) initial effects, (b) the degree and quality of implementation, mechanisms of change and contextual factors, and (c) potential cost savings of the intervention.

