#### Assignment of intervention

Allocation of wards as intervention or control ward was based on ward managers’ decision to participate in the intervention. Participants’ assignment will be determined by their wards’ assignment.

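### The cost comparison is a plain t-test that allows for neither ward clustering nor self-selected wards, so its false-positive rate would be well above nominal

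*Protocol article*

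**What the plan says.** The Objectives section lists as its third aim "c) potential cost savings of the intervention". The Data analysis section of the Economic evaluation names the test for it: "We will analyse differences (possibly after log-transformation) between the mean total costs using a t-test". It continues: "we will perform additional analyses according to gender, age groups, and cost weight using t-test, Mann–Whitney-U-test, and other statistical tests". Neither sentence mentions wards, the propensity score or covariate adjustment.

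Elsewhere the article recognises both features of the design:

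- **Assignment of intervention:** "Allocation of wards as intervention or control ward was based on ward managers’ decision to participate in the intervention", and "Participants’ assignment will be determined by their wards’ assignment".
- **Sample size** (for length of stay): three wards per arm with 120 patients each, and "an intraclass correlation coefficient of 0.05".
- **Evaluation of effects, Data analysis:** "We will use a propensity score approach (PSA) to balance individual characteristics between participants in intervention and control groups". The same paragraph says that clusters will at least be handled as fixed effects. Both statements stand under the evaluation of effects, not under the economic evaluation.
- **Discussion:** concedes a high risk of selection bias and says in general terms that baseline differences will be considered in the statistical analyses.

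**The concern.** A two-sample t-test on patient costs assumes that patients are independent and that the arms are comparable. The design gives no ground for either assumption. Patients on one ward share case mix and practice, and the cost variable is built from diagnosis-related group charges, which follow case mix directly. With only three wards per arm, differences between wards can dominate the error of the cost difference, and the t-test leaves them out. Because managers chose their arm, a case-mix difference between the arms would pass straight into the estimate.

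The optional log-transformation helps with skewness only. It also moves the comparison away from mean cost, which is the quantity that a hospital budget needs.

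What is at stake is that a chance or case-mix difference is called a saving or a loss more often than the nominal level suggests. The Discussion expects the results to inform decisions at management and policy level.

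**Working it through.** **Inputs from the article (Sample size):** three wards per arm, m = 120 patients per ward (360 per arm), ICC 0.05, SDs 18 and 16 days, difference 3 days, one-sided level 50%. The ICC and SDs are for length of stay.

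**Assumptions made here:** the cost test is two-sided at 5%; 360 patients per arm also enter the cost analysis; the cost ICC is unknown and is varied.

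**1. The plan's own figure.** Design effect = 1 + (120 − 1) × 0.05 = 6.95. Standard error = √[(18² + 16²) × 6.95 / 360] = 3.346 days. At a one-sided level of 50% the critical value is 0, so power = Φ(3 / 3.346) = 0.815. This reproduces the stated 81.5%, so the plan itself applies a design effect of 6.95 to length of stay.

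**2. True size of the unadjusted t-test.** False-positive rate = 2 × [1 − Φ(1.96 / √DE)], where DE = 1 + 119 × ICC.

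| ICC | DE | √DE (factor by which SE is understated) | False-positive rate |
|---|---|---|---|
| 0.005 | 1.595 | 1.26 | 12.1% |
| 0.01 | 2.19 | 1.48 | 18.5% |
| 0.02 | 3.38 | 1.84 | 28.6% |
| 0.05 | 6.95 | 2.64 | 45.7% |
| 0.10 | 12.9 | 3.59 | 58.5% |

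At ICC 0.05, 720 patients carry the information of 720 / 6.95 ≈ 104.

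**3. Simulation check** (8,000 runs, six wards of 120, ICC 0.05). The patient-level t-test rejected in 46.8% of runs with normal data. With skewed lognormal costs analysed untransformed (ICC set on the log scale) it rejected in 41.1%. A t-test on the six ward means, run on the normal data, rejected in 4.7%.

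**4. Adding a case-mix difference.** Assume that case mix makes intervention-ward costs 10% lower. With an assumed coefficient of variation of 1, this is 0.10 SD. The naive standard error is √(2/360) = 0.0745 SD, so the shift is 0.10 / 0.0745 = 1.34 naive standard errors. The probability of a significant false saving is 1 − Φ[(1.96 − 1.34) / √DE]:

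- without clustering (DE = 1): 1 − Φ(0.62) ≈ 27%;
- with ICC 0.05 (√DE = 2.64): 1 − Φ(0.23) ≈ 41%.

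Clustering alone at ICC 0.05 already gives about 45.7% / 2 ≈ 23% false savings, so the 41% is a joint effect.

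**5. Interval width** (95% half-width in SD units, ICC 0.05). Naive: 1.96 × √(2/360) = 0.146. Ward-level on 4 degrees of freedom: 2.776 × √(2 × 6.95 / 360) = 0.546.

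**The case against.** The strongest reply has four parts.

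- **The inputs are borrowed.** The ICC of 0.05 is for length of stay and none is given for costs. The economic section states no significance level, promises no confidence interval, and does not say how many claims records it will use. This stands. The size of the inflation is assumed, although even ICC 0.01 gives more than three times the nominal 5%.
- **Selection is not ignored altogether.** The Discussion's sentence on baseline differences is not limited to the clinical outcomes, and analyses by cost weight bear on case mix. This softens the selection half of the point. It does not adjust the named test and does nothing about clustering. Cost weight is also one of the measures compared between the arms in the cost-consequence analysis, so it is not a clean baseline covariate.
- **The trial is exploratory.** It is powered for direction of effect only, and costs are the third objective. This limits the severity. It is also a reason to prefer an estimate with an honest interval to a test that overstates certainty.
- **The unit of analysis is not stated.** That is so, but claims data, t-tests and Mann–Whitney tests with no mention of wards make the patient-level reading the natural one.

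A reader might infer that a spurious saving or loss is the likely result. The documents do not support that: the rate passes one half only towards ICC 0.10, and no cost ICC is given. Nor can 41% false savings be put down to case mix alone, since without clustering the figure is about 27%.

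**Conclusion.** The point holds as a should-fix. The article commits to a named test that fits neither the unit of assignment nor the way wards entered the arms, and its own sample-size section shows that its authors expect within-ward correlation. This is a stated choice, not detail left to a later plan.

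Under a two-sided 5% level and 120 patients per ward, the false-positive rate is about 18.5% to 46% for ICCs of 0.01 to 0.05. The upper figure rests on carrying the length-of-stay ICC over to costs. The case-mix figures rest on an assumed 10% shift and an assumed coefficient of variation of 1.

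It would go too far to conclude that the trial's main result is compromised. The primary outcome is analysed separately, and the cost analysis can be corrected before it is run without changing trial conduct.

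**What to change.** In the Data analysis section of the Economic evaluation, replace the t-test with a cluster-aware, case-mix-adjusted estimate of the difference in mean cost on the original scale. Two suitable forms are:

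- a comparison of adjusted ward mean costs, three against three, with a 95% confidence interval on 4 degrees of freedom; or
- a mixed model with ward as a random effect, case-mix covariates and a small-sample correction.

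Copying the fixed ward effects from the evaluation of effects would not work: wards are nested within arms, so a full set of ward effects is aliased with treatment.

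For adjustment, use the propensity score already planned if the pseudonymised claims records can be linked to study codes. The article does not say whether they can. If not, use the case-mix variables in the claims data that are fixed before treatment, such as gender and primary diagnosis. Label any patient-level test as descriptive only.

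The cost is a change of wording, a modest amount of analysis and possibly some linkage work. The interval becomes much wider, so a significant saving becomes unlikely. Adjustment for patient characteristics will also not remove differences in practice between self-selected wards, and the report should say so.

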## Dissemination

We will publish main study results in international, peer reviewed journals. In addition, we will present our results at relevant scientific conferences and meetings. We will report the results based on this study protocol as well as the recommendations of current reporting guidelines. Main study information (e.g., intervention material and results) will be freely available at our project website (https://www.enrole-acute.uni-koeln.de/).

We will share authorship between persons involved in the study following the current guidelines of the International Committee of Medical Journal Editors. Persons not directly involved in the study will not be granted authorship.

## Discussion

Complex interventions are considered most promising in promoting PCC [76]. The ENROLE-acute intervention builds on implementing an expanded nursing role as a core element to enhance PCC for people with cognitive impairment in acute care. Intervention development and testing are theory-based and follow recent guidance [26, 69]. The planned exploratory CCT will provide insights into the intervention’s initial effects, with the primary outcome focusing on patient length of hospital stay. Since there is a lack of high-quality studies to evaluate PCC interventions for people with cognitive impairment using expanded nursing roles in acute care, our study will provide important evidence. With the accompanying mixed-methods process evaluation, we will additionally examine the intervention’s implementation, mechanisms of change, and contextual factors. Analysing these underlying processes will lead to more transparency in trial results and a comprehensive understanding of how and under what circumstances the intervention will actually work. The additional economic analysis will increase our knowledge regarding the costs of the intervention.

However, some limitations of the study must be considered. Due to practical reasons, randomisation of the clusters will not be feasible. This may lead to differences between the groups at baseline resulting in a high risk of selection bias. However, we will consider these differences in the statistical analyses. Due to the nature of the intervention, blinding of participants and researchers during the study period will also not be possible. The knowledge of the group allocation might affect both the participants’ answers and data collection by researchers. At least the statistician will be blinded during data analysis. Finally, staff turnover during the six-month intervention period might result in differences between staff participating in the data collection at baseline and follow-up.

Despite the limitations, the study results will support the future development and implementation of new as well as the optimisation of existing PCC interventions based on expanded nursing roles. Our implications can particularly inform evidence-based decision making at the management and policy level. Additionally, our results will provide valuable information for planning and conducting large-scale trials as claimed in the third and fourth stage of the MRC guidance [26].

